**Fig. 1 Fig1:**
[figure not shown]
Study flow diagram

**Table 2 Tab2:** Table of times and events for adults and children over 12 years of age

Event	Screen/enroll day 1	Day 3^3^	Day 30^7^	Day 60^7^	Day 90^7^	Day 120^7^	Day 150^7^	Day 180^7^	Malaria diagnosis/ recurrence^2^
a. Informed consent	X								
b. Medical history	X								
c. Physical exam	X								X
d. Brief clinical evaluation and vital signs^1^			X	X	X	X	X	X	X
e. Malaria RDT, DBS, smear and PCR genotyping^6^	2 mL		1.5	1.5	1.5	1.5	1.5	1.5	1.5 mL
i. CBC	1 mL	1 mL^3^							
k. Molecular resistance markers^2^									6 mL
l. G6PD RDT, fluorescent spot, quantitative testing	1.5 mL								
m. Gametocyte PCR	2.5 mL		2.5	2.5	2.5	2.5	2.5	2.5	2.5 mL
n. Urine pregnancy test (women of child-bearing age)	X		X	X					X
o. Malaria treatment^4,5^	X		X	X					X
Daily phlebotomy (mL)	7	1^3^	4	4	4	4	4	4	10
Cumulative phlebotomy (approximately mL)	7		11	15	19	23	27	31	41

^1^Brief clinical evaluation includes an interval medical history, vital signs and a directed physical exam as indicated

^2^Performed only for volunteers with smear-positive malaria. Those with PCR-positive malaria will be treated following national guidelines but will not have blood drawn for molecular markers of resistance

^3^To be drawn for G6PD-deficient volunteers only. All G6PD-deficient volunteers with > 10% of Hgb or HTC drop on D3 will have CBC on day 7

^4^Patients screening positive on microscopy and/or PCR for *P. falciparum* malaria in the FSAT arm will receive currently recommended blood-stage antimalarials under published national treatment guidelines as well as single, low-dose primaquine (15 mg). Volunteers with *P. vivax* will be treated with the currently recommended blood-stage agent (DHA-PIP), as well as primaquine – G6PD-normal volunteers will receive 15 mg daily for 14 days, while G6PD-deficient volunteer will receive 45 mg × 8 weeks. All volunteers in the MMP arm will receive a fixed-dose 3-day course of DHA-piperaquine at 0, 24 and 48 h starting on days 1, 30, and 60, and a weekly 22.5-mg dose of primaquine for 12 weeks. All therapy will be directly observed

^5^For all volunteers with recurrent malaria, rescue therapy will be with the recommended agent(s) per national guidelines

^6^May be repeated as medically indicated (e.g., if patient is malaria-positive or otherwise ill on enrollment). An additional 0.5 mL will be collected on the day of enrollment for baseline G6PD genotyping

^7^Time window of ± 7 days

*CBC* complete blood count, *DBS* dried blood spot, *DHA-PIP* dihydroartemisinin-piperaquine, *G6PD* glucose-6-phosphatase dehydrogenase, *Hgb* hemoglobin, *PCR* polymerase chain reaction, *RDT* rapid diagnostic test

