Assess the effectiveness of presumptive anti-relapse and transmission-blocking therapy with weekly low-dose primaquine (22.5 mg)^a^	Incidence of *P. vivax* recurrent infection and PCR-corrected *P. falciparum* recrudescence^a^ PCR-corrected absence of gametocytemia^a^
Evaluate the safety and tolerability of blood-stage antimalarials and weekly low-dose primaquine at 12 weeks versus 8 weeks in treated MMP and FSAT volunteers, respectively	Number of hemolytic events or other serious adverse events in participants over 13 years of age receiving primaquine
Assess level of antimalarial drug resistance at the selected study sites	Number of all-species malaria recurrence, established molecular markers of drug resistance, and clinical failure rates based on WHO criteria
Define the proportion of asymptomatic carriers of malaria in the study population	Cumulative incidence and incidence density of PCR-corrected parasitemia and submicroscopic parasitemia in each arm
Define the epidemiology of malaria infection in volunteers developing malaria	Cumulative incidence and incidence density of parasitemia
Compare the sensitivity and specificity of the currently recommended malaria rapid diagnostic test of choice in Cambodia with RT-PCR	Retrospective assessment of the proportion of asymptomatic carriers that would have been missed by each test and an estimate of the incremental cost-effectiveness of each test
Compare sensitivity and specificity of two currently available rapid diagnostic tests to detect moderate to severe G6PD deficiency using quantitative G6PD testing as the reference standard	Retrospective assessment of the proportion of persons with moderate to severe deficiency who would have been missed with each screening modality, and an estimate of the cost-effectiveness of each test
Describe population demographics to include the acceptability of FSAT, malaria prophylaxis, and use of vector control measures among participants, including willingness to participate in future malaria elimination campaigns	Descriptive analysis of participants’ responses to survey questions pre and post study regarding FSAT, malaria prophylaxis, and use of vector control measures

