### Clinical procedures

Following documentation of informed consent/assent and determination of eligibility, a study physician completes an initial medical history and physical examination (Table 2). Volunteers aged 13 years and older have a rapid diagnostic test (RDT) for malaria, thick and thin blood films to estimate both sexual and asexual parasite densities, and malaria PCR diagnosis. Additional laboratory testing includes a complete blood count (CBC); an estimate of G6PD activity using quantitative testing to be compared with fluorescence and commercially available point-of-care testing; G6PD genotyping; real-time PCR to detect gametocytes; and analysis of molecular markers of resistance for those malaria positive at intake. Children aged 12 years and under have only rapid malaria diagnostic testing, malaria smears and PCR to detect submicroscopic parasitemia, with other testing deferred in children to reduce phlebotomy burden. Children less than 13 years of age are not tested for G6PD deficiency as they are not treated with PQ under this protocol. G6PD-deficient volunteers 13 years and older are counseled regarding the diagnosis, and have a repeat CBC on day 3 (± 1 day) following PQ treatment with repeat testing on day 7, if they have a greater than 10% drop in their hemoglobin or hematocrit, or at any time there are clinical signs of hemolysis.

All volunteers are followed monthly thereafter or at any time that they present with symptoms of suspected malaria, with a brief clinical evaluation and malaria diagnostics to include PCR assays for asexual and sexual parasites. Malaria-positive volunteers aged 13 years and older have additional tests for molecular markers of resistance. At these times, a swatch is taken from the volunteer’s uniform or clothing for repellency monitoring.

At the conclusion of the 180-day (− 2 to + 3 days) follow-up period, volunteers have blood drawn for malaria smears, RDTs, asexual blood-stage and gametocyte PCR diagnosis. If infection is noted at discharge, volunteers will continue to be followed until resolution of infection.

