### Halting rules criteria

Any volunteer with G6PD deficiency who experiences grade 3 hemolysis following PQ administration will be discontinued from the use of PQ and monitored closely. If more than three subjects with G6PD deficiency are found to have grade 3 hemolysis following treatment with PQ for anti-relapse therapy, further treatment with PQ will be suspended for all G6PD-deficient subjects enrolled in the study.

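### Table 2 ties the hemolysis CBC to study day 3, while Clinical procedures ties it to primaquine treatment. If sites follow the table, G6PD-deficient FSAT volunteers treated after enrolment have no scheduled post-primaquine CBC.

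*Protocol article*

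**What the plan says.** Table 2 has CBC entries on day 1 and day 3 only; the malaria diagnosis/recurrence column marks treatment but no CBC. Footnote 3 says the day-3 sample is "To be drawn for G6PD-deficient volunteers only" and adds: "All G6PD-deficient volunteers with > 10% of Hgb or HTC drop on D3 will have CBC on day 7". Neither the row nor the footnote refers to primaquine.

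Clinical procedures says that G6PD-deficient volunteers aged 13 years and older "have a repeat CBC on day 3 (± 1 day) following PQ treatment with repeat testing on day 7" after a hemoglobin or hematocrit drop above 10%, "or at any time there are clinical signs of hemolysis". This sentence is not limited to one arm or to enrolment.

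On exposure, footnote 4 of Table 2 starts DHA-piperaquine in MMP on days 1, 30 and 60 and adds "a weekly 22.5-mg dose of primaquine for 12 weeks". In FSAT, primaquine follows a positive smear or PCR, at screening or at a monthly visit (Treatment intervention; Table 2, footnote 4).

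The Table 1 safety objective sets the two arms side by side on this endpoint: "Number of hemolytic events or other serious adverse events in participants over 13 years of age receiving primaquine". The halting rules stop primaquine for "Any volunteer with G6PD deficiency who experiences grade 3 hemolysis following PQ administration", and suspend it for all G6PD-deficient subjects once more than three have had grade 3 hemolysis after anti-relapse primaquine.

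**The concern.** The purpose of the CBC is to detect a fall in hemoglobin after primaquine, so the day from which it is counted decides whether it can do so. A fixed study day works for a regimen that starts at enrolment. It does not work for one that starts when an infection is found. Because the arms differ in exactly this respect, a literal reading of Table 2 would look for hemolysis after the first dose in one arm and, for part of the other arm, before any dose. A difference in laboratory-detected events could then reflect when blood was drawn rather than the regimens. The halting rule would also be fed by incomplete counts from late-treated FSAT volunteers.

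A smaller mismatch affects the same endpoint. Table 1 counts participants over 13 years of age, whereas Study design and Treatment intervention give primaquine from age 13. Read literally, 13-year-olds are dosed but not counted.

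**Working it through.** **Step 1: the two schedules applied to the four situations that can arise** (G6PD-deficient, aged 13 or older).

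| Situation | Table 2 with footnote 3 | Clinical procedures |
|---|---|---|
| MMP, first primaquine on day 1 (assumed) | CBC on day 3, after primaquine | Same |
| FSAT, positive at screening, primaquine from day 1 | CBC on day 3, after primaquine | Same |
| FSAT, first positive at a day 30 to day 180 visit | CBC on study day 3, before any primaquine; none scheduled afterwards | CBC on day 3 (± 1 day) after primaquine |
| FSAT, never positive | CBC on day 3 with no primaquine given | No post-primaquine CBC needed |

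The first row rests on an assumption: footnote 4 dates the start of DHA-piperaquine but not of the first weekly primaquine dose.

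**Step 2: the gap in the third row.** Nominal interval from the Table 2 CBC to the earliest late FSAT treatment: 30 − 3 = 27 days. With the ± 7-day visit window: 23 − 3 = 20 days. For an infection found at the nominal last visit: 180 − 3 = 177 days.

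**Step 3: what the blood volumes can and cannot show.** Table 2's totals reproduce.
- Day 1: 2 + 1 + 1.5 + 2.5 = 7 mL.
- Malaria diagnosis/recurrence: 1.5 + 6 + 2.5 = 10 mL.
- Cumulative: 7 + 6 × 4 + 10 = 41 mL.

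The cumulative row leaves out the 1 mL day-3 draw (7 + 4 = 11 at day 30), and the conditional day-7 CBC has no column. The totals therefore omit conditional draws that the plan does intend, and they do not settle which schedule governs.

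**Step 4: the halting count.** More than three cases means the rule acts at the fourth. If four occur and one, visible only in a blood count, is not drawn, the count is 4 − 1 = 3 and the rule does not act.

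**The case against.** The strongest reply is that Clinical procedures already provides the CBC. It counts from primaquine, applies to both arms and adds testing whenever there are clinical signs. A site that follows the text gives late-treated FSAT volunteers the same first check as MMP volunteers. This stands, and it makes the problem conditional on sites working from Table 2. It does not remove the contradiction, since both schedules are printed and a schedule of events is a natural working document at a site.

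Several stronger readings are tempting but unsupported:
- A reader might infer that FSAT volunteers get no CBC, or that the arms' hemolysis counts are already not comparable. The text contradicts the first. The second is only a risk, and the endpoint also counts other serious adverse events and is not defined by the scheduled CBC.
- A reader might take the 10 mL diagnosis total as proof that no CBC is planned. A sample taken three days after a dose would not fall on the diagnosis day, so its absence there is expected.
- A reader might treat the gap as covering the whole FSAT arm. It does not: primaquine can start on day 1 in FSAT, and G6PD-normal volunteers have no scheduled post-primaquine CBC in either arm.
- A reader might object to how few weekly doses are followed by a CBC. That is a view on monitoring frequency, not a contradiction.
- A reader might infer that adverse event data alone will decide feasibility. Limitations names diagnostic and adverse event data together.

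It is also fair to say that safety is a pilot secondary endpoint, that the primaquine regimens already differ between arms, and that details of the safety analysis may sit in a plan not shown.

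**Conclusion.** The point holds in conditional form. Table 2 with footnote 3 and Clinical procedures give different anchors for the same safety test. If Table 2 is followed literally, G6PD-deficient FSAT volunteers aged 13 and older whose primaquine starts after enrolment have no scheduled post-primaquine CBC and are tested only on clinical signs. Laboratory-detected hemolysis could then be under-ascertained in FSAT relative to MMP, which affects the Table 1 comparison and the halting count.

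This rests on two assumptions: that some sites use the table rather than the text, and that MMP primaquine starts on day 1. The size cannot be stated, because the article gives neither the prevalence of G6PD deficiency nor the expected number of late FSAT treatments. The age mismatch is certain as wording but small, affecting at most one year of age. Nothing here says which CBC schedule is clinically right.

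**What to change.** 1. Reconcile Table 2 (CBC row, footnote 3, malaria diagnosis/recurrence column and blood volumes) with Clinical procedures, so that one anchor applies in both arms. The clinical team should choose it.
2. Compare hemolysis between arms over the same interval from each volunteer's first primaquine dose.
3. Reconcile the age limit in the Table 1 safety endpoint with dosing from 13 years in Study design and Treatment intervention.

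The cost is mostly wording. If the reconciled schedule has a 1 mL CBC after late primaquine, as Clinical procedures already states, each affected episode takes 1 mL more than Table 2 shows: 10 + 1 = 11 mL if booked to that column, and 41 + 1 = 42 mL cumulative (43 mL if the study-day-3 draw is also counted). The second change is a choice of analysis window and needs no new data beyond dose and sample dates.

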**Fig. 2. Fig2:**
[figure not shown]
Study timeline for monthly malaria prophylaxis (MMP) intervention clusters. *Treat with artesunate and mefloquine. *DHA-PIP* dihydroartemisinin-piperaquine, *GC* gametocyte, *RDT* rapid diagnostic test, *PCR* polymerase chain reaction, *G6PD* glucose-6-phosphatase dehydrogenase, *CBC* complete blood count

### Clinical procedures

Following documentation of informed consent/assent and determination of eligibility, a study physician completes an initial medical history and physical examination (Table 2). Volunteers aged 13 years and older have a rapid diagnostic test (RDT) for malaria, thick and thin blood films to estimate both sexual and asexual parasite densities, and malaria PCR diagnosis. Additional laboratory testing includes a complete blood count (CBC); an estimate of G6PD activity using quantitative testing to be compared with fluorescence and commercially available point-of-care testing; G6PD genotyping; real-time PCR to detect gametocytes; and analysis of molecular markers of resistance for those malaria positive at intake. Children aged 12 years and under have only rapid malaria diagnostic testing, malaria smears and PCR to detect submicroscopic parasitemia, with other testing deferred in children to reduce phlebotomy burden. Children less than 13 years of age are not tested for G6PD deficiency as they are not treated with PQ under this protocol. G6PD-deficient volunteers 13 years and older are counseled regarding the diagnosis, and have a repeat CBC on day 3 (± 1 day) following PQ treatment with repeat testing on day 7, if they have a greater than 10% drop in their hemoglobin or hematocrit, or at any time there are clinical signs of hemolysis.

All volunteers are followed monthly thereafter or at any time that they present with symptoms of suspected malaria, with a brief clinical evaluation and malaria diagnostics to include PCR assays for asexual and sexual parasites. Malaria-positive volunteers aged 13 years and older have additional tests for molecular markers of resistance. At these times, a swatch is taken from the volunteer’s uniform or clothing for repellency monitoring.

At the conclusion of the 180-day (− 2 to + 3 days) follow-up period, volunteers have blood drawn for malaria smears, RDTs, asexual blood-stage and gametocyte PCR diagnosis. If infection is noted at discharge, volunteers will continue to be followed until resolution of infection.

### Laboratory procedures

#### Microscopy

Stained thick and thin blood smears are examined by two microscopists blinded to each other’s results and to the treatment status of the study volunteer. Two blood smears are made for every enrolled volunteer. Slide 1 is stained immediately and examination of Giemsa-stained thick and thin smears made. This slide is stored in a different box from slide 2, which is only read if there is a problem with the first slide.

Parasite densities are calculated based on a count of parasites per 200 white blood cells (WBCs) (thick film) or for low parasitemias (e.g., 10 parasites/μL), per 500 WBC or 5000 red blood cells (RBCs) (thin film). Both asexual and sexual stages are enumerated. A total of 200 oil immersion fields are examined on the thick film before a blood smear is considered negative. The final count is determined by taking the geometric mean of the two counts. In case of a difference in results (positive/negative; species diagnosis) between the two microscopists, the blood smear is re-examined by a third microscopist blinded to the results of the first two readers and the treatment regimen, and the third reading is accepted as the final result.

Malaria microscopy results is confirmed using real-time PCR correction for the detection of *P. falciparum* and *P. vivax* using 18S ribosomal ribonucleic acid (RNA) (*18S rRNA*) genes unique to each species. Parasite deoxyribonucleic acid (DNA) will be isolated from approximately 200–250 μL of venous or capillary blood collected in an EDTA microtube.

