### Aim and objectives

We present a pilot operational research protocol to investigate the effectiveness of monthly prophylactic drug administration compared to a focused screen-and-treat approach to inform a regional malaria elimination initiative by the Royal Cambodian Armed Forces (RCAF).*Primary objective*: to compare the effectiveness of focused screening and treatment (FSAT) following current national treatment guidelines versus monthly malaria prophylaxis (MMP) with dihydroartemisinin-piperaquine (DHA-PIP) in combination with weekly primaquine (PQ) (22.5 mg) as transmission-blocking and radical curative agent to reduce the risk of malaria infection in personnel residing in military encampments on the Thai-Cambodian border*Secondary objectives*:◦ To estimate the incremental benefit of wearing a permethrin insecticide-treated uniform (ITU) over drug therapy and existing vector control interventions compared to a sham insecticide-treated uniform (sITU) treated with water. Civilian participants will have comparable selected outer garments treated◦ To define the proportion of asymptomatic carriers of malaria in the population, including the cumulative incidence and incidence density of microscopic and submicroscopic blood-stage parasitemia and gametocytemia◦ Additional secondary objectives can be found in Table 1/Additional file 1

**Table 1 Tab1:** Outcomes

Objectives	Outcomes/endpoints
Primary	
To compare the effectiveness of focused screening and treatment (FSAT) following current national treatment guidelines versus targeted monthly malaria prophylaxis (MMP) with DHA-piperaquine in combination with low-dose weekly primaquine (PQ) (22.5 mg) for 12 weeks	Absolute risk reduction in a cluster based on those individuals’ polymerase chain reaction (PCR)-corrected absence of parasitemia at the end of 6 months in the MMP versus FSAT clusters
Secondary	
Estimate the incremental benefit of insecticide-treated uniforms (ITU) over drug therapy and existing vector control interventions compared to a sham insecticide-treated uniform (sITU)^a^	Absolute risk reduction in a cluster based on those individuals’ PCR-corrected absence of parasitemia at the end of 6 months^a^ Proportional landings of mosquitoes on treated uniform’s swatch side of cages

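### The thin-film option of 5000 red cells cannot measure the low parasitemias it is offered for, and the geometric mean with a stage-blind third-reader trigger can set a final gametocyte count to zero although one reader saw gametocytes.

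*Protocol article*

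**What the plan says.** All the rules are in the protocol article, Laboratory procedures, Microscopy.

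- **Standard count:** "Parasite densities are calculated based on a count of parasites per 200 white blood cells (WBCs) (thick film").
- **Low-density count:** "for low parasitemias (e.g., 10 parasites/μL), per 500 WBC or 5000 red blood cells (RBCs) (thin film"). The two denominators are offered as alternatives, with nothing to say when each applies.
- **Stages:** "Both asexual and sexual stages are enumerated".
- **Negative smear:** "A total of 200 oil immersion fields are examined on the thick film before a blood smear is considered negative". This is separate from the density count.
- **Combining the readers:** "The final count is determined by taking the geometric mean of the two counts". No rule for a zero is given.
- **Third reader:** called "In case of a difference in results (positive/negative; species diagnosis) between the two microscopists". That reading then becomes final.

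The smear results are used elsewhere in the article. Clinical procedures says the films serve to estimate both asexual and sexual densities. Aim and objectives plans the "cumulative incidence and incidence density of microscopic and submicroscopic blood-stage parasitemia and gametocytemia". Statistical methods brings all parasitological data into the parasitological analyses. The primary endpoint and the Table 1 gametocyte endpoint rest on PCR.

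**The concern.** There are two separate faults.

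First, the section gives its own example of a low parasitemia and then permits a count too small to see it. A laboratory that chose the red-cell option would record either no density or, on the rare slide with one parasite in the counted cells, a density about a hundredfold too high.

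Second, a product containing a zero is zero, so the geometric mean lets one reader's zero cancel the other reader's positive count. The third reader would catch this if the disagreement counted as positive against negative. But positivity is judged on the whole smear over 200 fields, and the trigger lists only positive/negative and species. If both readers call the smear positive for the same species, for instance on asexual parasites, and only one counts gametocytes, no listed trigger applies.

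At stake are the smear densities, and the microscopic gametocytemia figure if gametocyte presence is read from the final count. These losses would fall at low density, the range of interest in a study of largely asymptomatic infection.

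**Working it through.** **Inputs from the article:** example density 10/µL; denominators of 200 or 500 white cells or 5000 red cells; 200 fields; two readers and a geometric mean.

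**Assumptions, not in the article:** 4–5 million red cells/µL; 6000–10000 white cells/µL; 0.002 µL of blood per oil immersion field (range 0.001–0.0025); Poisson counts; independent readers. The 50/µL density is illustrative.

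**1. Density represented by one counted parasite** = cells per µL / cells counted.
- 500 white cells: 6000/500 = 12/µL to 10000/500 = 20/µL. This agrees with the 10/µL example in order of magnitude, and exactly at 5000 white cells/µL (5000/500 = 10).
- 5000 red cells: 4,000,000/5000 = 800/µL to 5,000,000/5000 = 1000/µL. This is 80 to 100 times the example.

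**2. Expected count at 10/µL on 5000 red cells:** m = 10 × 5000/5,000,000 = 0.010, or 10 × 5000/4,000,000 = 0.0125. The chance that a reader counts none is exp(−m) = 0.990 or 0.988.

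**3. Chance that a positive smear has a zero count.** At 10/µL the 200-field search expects 10 × 200 × 0.002 = 4 parasites (2–5 over the range). A reader finds at least one with probability 1 − exp(−4) = 98% (86–99%). Agreement that the smear is positive is therefore likely even where the density count is zero.

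**4. Geometric mean, no third reading.** With P0 = exp(−m), the final count is zero with probability 1 − (1 − P0)², and both readers count zero with probability P0².

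| Density, on 500 white cells | White cells/µL | m | P0 | Final zero | Both zero |
|---|---|---|---|---|---|
| 10/µL | 6000 | 0.833 | 0.435 | 68% | 19% |
| 10/µL | 10000 | 0.500 | 0.607 | 85% | 37% |
| 50/µL | 6000 | 4.17 | 0.016 | 3% | under 0.1% |
| 50/µL | 10000 | 2.50 | 0.082 | 16% | 0.7% |

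The gap between the last two columns is due to the averaging rule, not to the blood sample.

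**5. If every zero/non-zero split in the density count went to the third reader,** whose zero would be final, the probability of a final zero is P0² + 2·P0²·(1 − P0). At 10/µL and 8000 white cells/µL, m = 0.625 and P0 = 0.535, so this is 0.287 + 2 × 0.287 × 0.465 = 55%. The geometric mean alone gives 78%. An arithmetic mean gives 29%, because it is zero only when both counts are.

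**6. If presence is judged over the 200 fields and splits go to the third reader,** the same formula with P0 = exp(−4) = 0.018 gives 0.1% declared absent at 10/µL. At 0.0025 and 0.001 µL per field it is 0.01% and 5%.

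**The case against.** The strongest reply is that little depends on this. The primary endpoint and the Table 1 gametocyte endpoint are PCR-based, and treatment follows smear or PCR positivity, not density. That stands and limits the point.

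The 500-white-cell count is already permitted, so the near-certain zero applies only where the red-cell option is chosen. That also stands. The fault is offering the two as equivalents.

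The word for results in the third-reader sentence could cover each enumerated stage. That reading is open, but the trigger does not say so. Applied to the density counts, it would still leave about 55% at zero in step 5.

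A journal article may leave the handling of zeros to a laboratory manual. That is fair for the missing zero rule alone. The red-cell option beside a 10/µL example, the geometric mean and the listed triggers are stated text.

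Three stronger readings are tempting and not supported:
- **Positive smears become negative, or carriers are necessarily reclassified as submicroscopic.** Negativity rests on the 200 fields, and nowhere is gametocyte carriage defined as a final density above zero. Reclassification follows only if presence is taken from the final count.
- **Low-density smears as a rule end at zero.** This depends on density and denominator; at 50/µL on 500 white cells it is 3–16%.
- **At 50/µL, 34–60% of gametocyte counts are lost.** That uses the standard 200-white-cell denominator (m = 1.67 to 1.0), not the low-parasitemia count.

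**Conclusion.** The point holds within these limits. The 5000-red-cell option misses the article's own example by a factor of 80–100, and no plausible red-cell count rescues it. The geometric mean and the stage-blind trigger together allow a final gametocyte count of zero on a slide where one reader counted gametocytes. At 10/µL on 500 white cells this adds about 48–49 percentage points of zeros beyond those where both readers count none (68 − 19 and 85 − 37). At 50/µL it adds about 3–15 points.

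The percentages rest on the assumed cell counts and on independent Poisson readers. Both work from the same slide, so if they count overlapping cells the gap shrinks. The article does not show which densities are typical. The consequence is confined to smear densities and microscopic gametocytemia. It is worth correcting because the correction is cheap, not because it threatens the main comparison.

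**What to change.** 1. Confine the 5000-red-cell thin-film count to high parasitemias. For low ones, count on the thick film against at least 500 white cells.
2. Apply the positive/negative discordance rule separately to asexual stages and gametocytes. Judge presence over the 200 fields already read, and send splits to the existing third reader.
3. Where both readers agree that a stage is present but one density count is zero, use the arithmetic mean. The two remedies then do not overlap: the third reader settles presence and the mean settles density.

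The cost is laboratory wording and somewhat more third readings. With P0 from the 200-field search, a split has probability 2·P0·(1 − P0): about 4% of slides with gametocytes at 10/µL (1–23% over the field-volume range), and never more than half at lower densities. Some zeros remain at 10/µL, since both readers still count none on 500 white cells in 19–37%, but such a slide stays recorded as positive for that stage.
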